### Plans for communicating important protocol amendments to relevant parties

Ethical approval to conduct this study has been granted by the Hospital Universitario de Navarra Research Board (PI_2021/39). If relevant, current participants will be informed of protocol modifications. The ClinicalTrials.gov registry for this study will be updated with important protocol amendments.

### Data collection and management

Completed personal data or other documents containing protected personal health information will be kept in a locked file at the principal investigator office in the Hospital Universitario de Navarra. Data will be entered into an electronic de-identified database by authorized study team members, and checked for completeness and accuracy. Access to data with identifiers will be restricted to authorized study team members and authorities. Any data required to support the protocol can be supplied on request. Identifiable data will be destroyed 10 years after study finalization or 5 years after the last publication.

The datasets analyzed during the current study and statistical code are available from the corresponding author on reasonable request, as is the full protocol.

Adherence to training in the intervention group will be monitored by exercise trainers who will track attendance in training sessions. If participants miss any training sessions, they will be offered make-up sessions to complete the full 8 sessions of training. In both groups, in order to ensure attendance at the consultation, they are informed of the appointment by telephone and by letter.

### Detail description

Participants will be randomly assigned to the following groups:

Usual care group (control):

Participants randomly assigned to the usual care group will receive normal hospital care based on the Enhanced Recovery After Surgery (ERAS) protocol [31], including physical rehabilitation when needed.

Multicomponent exercise group (intervention):

The intervention will consist of a multicomponent physical training programme, which will include progressive and supervised endurance, resistance and balance training for 4 weeks, twice weekly sessions with a total of 8 sessions.

The supervised multicomponent exercise training programme will be comprised of 5 min of endurance training on a cycle ergometer, followed by upper and lower body resistance exercises, tailored to the functional capacity of the individual, using weight machines and with the goal of 2–3 sets of 8–10 repetitions at an intensity of 40–60% of 1 maximal repetition (1RM) (Matrix, Johnson Health Tech, Ibérica, SL, Madrid, Spain) combined with balance exercises and stretching. Each resistance training session will include chair squat and hip abduction exercises, as well as training on variable resistance machines with two exercises for the lower extremities (leg press and knee extension) and two exercises for the upper extremities (seated chest press and seated row). The training protocol is shown in Table 1.

**Table 1 Tab1:**
[figure not shown]
Intervention group exercise

One repetition maximum

Forward (to the right) and back (to the left) twice

Study staff will collect all adverse events that will be noted, which includes any event that occurs during or up to 15 min, after intervention, and persists despite therapy interruption and constitute criteria for discontinuing intervention. Severe adverse events will be promptly reported to the Regional Ethics Committee of the HUN. Management of adverse effects will be based on participant protection and safety.

If participants desire to stop training or develop health conditions or injury that precludes safe participation of exercise over the course of the intervention, they will be excluded from the study. 

Participants in either the intervention or control group will be asked to not participate in another structured exercise regimen or intervention over the course of their participation; otherwise, they will not be allowed to continue participation.

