## Opportunity of the trial/discussion

Functional decline and impaired quality of life are the main adverse outcomes of urgent surgery in the elderly patients. A high percentage of patients lose their autonomy, increasing the need for care at home and even the patient’s institutionalization in a postoperative rehabilitation clinic. All this translates into a psychological impact for the patient and his or her environment and in a considerable unquantified increase in health spending.

All the current evidence from international organizations’ works reminds us that the most important thing in the elderly is to focus attention and health care on the maintenance of intrinsic capacity, that is, its functional capacity.

However, surgeons are focused on medical-surgical problems during hospitalization, being less attentive to functional recovery, which would require longer hospital stays and would greatly increase healthcare costs.

The rehabilitation programme that we are proposing in this study could be applied in daily clinical practice, incorporating elderly patients undergoing urgent abdominal surgery into protocolized and standardized rehabilitation programmes with postoperative physical activity.

An important aspect of our trial is the inclusion of elderly patients after an urgent abdominal surgery; the majority of trials with aged frail participants excluded the patients with a recent surgery; however, the surgery is a major factor in the loss of functionality. This trial could demonstrate that a supervised multicomponent exercise training programme adapted to each patient can be performed safely after emergency surgery and could improve functional results.

If our hypothesis is correct, this project could show that individualized and progressive exercise programme provides effective therapy for improving the functional capacity and achieve a better functional, cognitive and quality of life recovery. This measure, without entailing a significant expense for the administration, probably has an important repercussion both in the short and long term, improving care and functional parameters and could determine a lower subsequent need for health resources. To verify this, we will carry out a cost-effectiveness study.

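### The only adverse-event description is tied to exercise sessions: read restrictively, it misses transient and delayed harms and cannot apply to controls

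*Protocol article*

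**What the plan says.** The adverse-event text follows Table 1 in the Detail description section of the protocol article. It opens broadly: "Study staff will collect all adverse events that will be noted". The same sentence then says that these include "any event that occurs during or up to 15 min, after intervention, and persists despite therapy interruption and constitute criteria for discontinuing intervention". The next sentence adds "Severe adverse events will be promptly reported to the Regional Ethics Committee of the HUN", with no arm, time window or definition of severity. The following paragraph says that participants who wish to stop training, or who "develop health conditions or injury that precludes safe participation of exercise over the course of the intervention, they will be excluded from the study".

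The exercise arm trains "for 4 weeks, twice weekly sessions with a total of 8 sessions". For controls, the section says: "Participants randomly assigned to the usual care group will receive normal hospital care based on the Enhanced Recovery After Surgery (ERAS) protocol". Rehabilitation is given to them if needed, but there are no study sessions.

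Safety is not among the primary or secondary outcomes. Even so, the section on the opportunity of the trial says the trial could demonstrate that the supervised programme "can be performed safely after emergency surgery and could improve functional results".

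**The concern.** A harm count is informative about an intervention when the same kinds of event are sought in the same way in both arms. Here the one operational description depends on a training session having just taken place. Staff who follow it would log a narrow class of events in the exercise arm and nothing comparable in the control arm.

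The population is aged 70 or over and is doing loaded resistance work within weeks of urgent abdominal surgery. Falls, next-day musculoskeletal problems, wound or abdominal-wall events and later cardiovascular events are all plausible. None needs to occur within 15 minutes of a session. If they are not sought, the safety statement in the discussion would have thinner support than a reader would expect from a randomised trial.

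**Working it through.** **1. The plan's own figures.** The article gives no safety figure. Its group sizes are needed below, so they were checked.
- Inputs (Sample size and statistical analysis section): SD 2.5, correlation 0.6, difference 1 point, type I error 0.05 (taken as two-sided), power 90%, ANCOVA.
- Residual SD = 2.5 × √(1 − 0.6²) = 2.0.
- n per group = 2 × (1.960 + 1.282)² × 2.0² / 1² ≈ 84.1, rounded up to 85. The article states 87, at which power is 91%.
- With 20% losses: 87 / 0.80 = 108.75, so 109 per group and 218 in total, as stated.

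Nothing in this point changes these numbers.

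**2. What the description covers on the restrictive reading.** An event must (a) fall within a session or the 15 minutes after it, (b) continue after the session is interrupted, and (c) amount to grounds for discontinuing.
- A faint or rhythm disturbance that resolves once the session stops fails (b).
- A fall at home, a joint injury noticed the next day or a wound problem hours later fails (a).
- Any event in a control patient fails (a), because there is no session.

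The grammar of (c) is uncertain: the plural verb may mean that such events are grounds for stopping, not that an event must be grounds for stopping before it is recorded. Dropping (c) as a condition changes none of the three results.

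**3. What is collected in both arms.** From the Secondary outcome measure section and the assessment table:
- Clavien-Dindo and Comprehensive Complication Index: admission and month 1.
- Mortality: admission and months 1, 3 and 6.
- Readmissions, nursing-home admissions and general-practitioner visits: months 1, 3 and 6.

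These support a randomised comparison of major harms. Falls and musculoskeletal injury are not named, complications are not scheduled after month 1, and resource use is listed without cause.

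**4. What an empty session log would show.** With zero events in n trained patients, the exact one-sided 95% upper bound on the risk per patient is 1 − 0.05^(1/n).
- n = 109 (all allocated): 1 − 0.05^(1/109) = 2.7%.
- n = 87 (after the planned 20% losses): 1 − 0.05^(1/87) = 3.4%.

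Both bounds refer only to session events as described and have no control rate beside them.

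**5. The exclusion sentence.** The article does not say whether exclusion after injury or illness ends follow-up. If it does, some exercise patients with harm outside the 15-minute window would be neither logged nor seen at later visits. That also sits uneasily with the intention-to-treat statement in the statistical section.

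**The case against.** A reader might infer that controls have no adverse events by definition, and that the trial therefore cannot say anything about safety. The documents do not support either statement.

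- The sentence begins with all adverse events and continues with a word meaning inclusion, so the 15-minute description can be read as one category among others. That stands. The broader reading, however, comes with no other window, definition or control-arm procedure, so staff could reasonably follow either.
- The severe-event sentence carries no session limit and no arm limit. That stands too, though it concerns reporting to the ethics committee and leaves severity undefined.
- Mortality, complications, readmissions, nursing-home admissions and general-practitioner visits are collected in both groups. Complications are assessed at month 1, around the end of the four-week programme, and general-practitioner visits give some information on non-admitted problems afterwards. This is real randomised evidence on harm and rules out saying that the trial cannot support a safety statement.
- The safety statement is conditional and largely about whether the sessions can be carried out. In-session monitoring partly answers that.
- The hours covered by the 15-minute windows are not a useful measure of size. Session length is not in the readable text, and exertional events cluster around sessions, so a share of time is not a share of risk.
- The full protocol is available on request and may hold event forms that an article would not print. Their absence from the article is no fault. What remains is that the article states a description narrower than the promise in the same sentence.

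**Conclusion.** The point holds as one of a badly fixed rule. The sentence promises all adverse events and specifies a narrow, session-bound subset. On the restrictive reading it yields an effectively one-arm count that omits transient and delayed events. The safety statement would then rest on the session log, which has no comparator, and on two-arm secondary outcomes that do not name falls or musculoskeletal injury and give no cause for visits.

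The size of any under-count cannot be estimated, because the article gives no event rates. An empty session log would exclude a risk above 2.7% (n = 109) or 3.4% (n = 87), assuming every patient counted was trained and observed. The conclusion depends on the restrictive reading of the event sentence. On the broad reading, the defect is only that the rule to follow is not stated. The primary analysis and the sample size are unaffected. The change is worth making but is not critical to the trial's main question.

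**What to change.** 1. Keep the 15-minute log and label it session-related events, reported for the exercise arm only.
2. Separate the definition of a recordable event from the discontinuation wording and reconcile the two, without changing any discontinuation rule. State whether participants excluded after injury or illness are still followed for harms.
3. At the existing month 1, 3 and 6 visits, ask both arms the same neutral questions about serious adverse events, falls, musculoskeletal injury, wound or abdominal-wall events and cardiovascular events since randomisation or the last visit. Have the blinded assessment staff ask them. Patients know their group, and the exercise arm has eight extra contacts, so events learned of only at sessions should stay in the session log.
4. Report patients with at least one event by allocated arm, with a risk difference and 95% CI.

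Cost: a few minutes per visit, one safety table and an amendment, for which the article already describes a communication route. Recruitment has been open since March 2022, so for patients whose visits are complete these data would be missing or retrospective. Ascertainment before and after the amendment should therefore be reported separately.

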## Methods/design

### Study design

This study is a parallel group, two-arm, superiority randomized trial with 1:1 allocation ratio, is monocentric and is conducted in the Department of Surgery of a tertiary public hospital in Navarra (Hospital Universitario de Navarra), Spain. Patients undergoing urgent abdominal surgery who meet inclusion criteria will be randomly assigned to the intervention or control group.

Patient recruitment will begin in 4 days after the surgical procedure, and these patients will be identified through the list of patients admitted to the hospital and assigned to the Department of General Surgery. Prior to randomization, the investigators will review the contraindications to participate in the exercise programme and will provide general information about the study. After signing an informed consent form, the subjects will be chosen randomly. 

Randomization will be performed by applying http://www.randomizer.org/. The doctor who decides the inclusion in the intervention or control group will not be the attending physician. Patients will be informed of the random inclusion in one of the groups.

The information in both groups is obtained in four different stages: the initial visit and at months 1, 3 and 6 after hospital discharge.

The protocol employs relevant standard protocol items for clinical trials according to the SPIRIT 2013 statement [29] and follows the CONSORT statement [30] for transparent reporting.

The trial is registered at ClinicalTrials.gov, identifier NCT05290532.

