**Fig. 1 Fig1:**
[figure not shown]
Inclusion and exclusión criteria, groups and follow-up

The exclusion criteria are (Fig. 1):Severe dementia (GDS 7)Unwillingness to either complete the study requirements or to be randomized into control or intervention groupUnstable cardiovascular disease or other unstable medical conditionMyocardial infarction in the past 3 monthsTerminal illnessChronic kidney disease: dialysisUpper or lower extremity fracture in the past 3 monthsEviscerationPatients transferred to a rehabilitation clinic prior to home discharge

If the patient throughout the study presents any of the exclusion criteria and wishes to leave the study, they will be removed from the study.

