### Sample size and statistical analysis

Assuming a type I error of 0.05, a correlation between pre and post-intervention values of the Short Physical Performance Battery (SPPB) of *r* = 0.6 and a standard deviation for the SPPB of 2.5, the required sample size to detect with a power of 90% a minimum difference of 1 point between groups in the change of SPPB score is 87 patients per group [27]. Assuming losses of 20%, the final objective of the size of each group is 109 patients, and, consequently, a total sample size will be 218 subjects. For the estimation, an ANCOVA method for the analysis of the differences has been considered. The outcome variables will be analyzed using mixed models, without missing data imputation. If the proportions of missing data are very large (more than 40%) on important variables, then trial results will be considered as hypothesis-generating results.

Baseline values will be compared by group using descriptive statistics as mean and standard deviation or median and interquartile range for quantitative variables and frequencies and percentages for categorical ones. To determine the efficacy of the intervention in the quantitative variables, such as the SPPB, we will use ANCOVA models, using post-intervention value as dependent variable, group study as the principal effect and pre-intervention value as covariate. If relevant group differences were observed at baseline, we would adjust for these variables in the model. In the case of qualitative or categorized variables (such as whether an improvement of a given magnitude between pre and post-intervention has been achieved or not), comparisons between groups will be conducted with the chi-square test or Fisher’s test, and complemented with logistic regression if additional adjustment is needed.

The level of statistical significance will be 0.05. Data will be analyzed using an intention-to-treat approach and using SPSS and R statistical software.

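### Intervention patients who stop training or become unfit for it are excluded from the study itself, a one-sided, health-related loss of outcomes that conflicts with the stated intention-to-treat analysis

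*Protocol article*

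**What the plan says.** The protocol article, Sample size and statistical analysis, fixes the analysis principle: "Data will be analyzed using an intention-to-treat approach". The same section specifies mixed models without imputation, and an ANCOVA of the post-intervention value on group and the pre-intervention value.

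Under Detail description, in the text after Table 1, two rules end participation after randomisation:

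- One sentence with two triggers. It opens "If participants desire to stop training" and goes on to those who "develop health conditions or injury that precludes safe participation of exercise over the course of the intervention, they will be excluded from the study".
- Both arms are asked not to join another structured exercise regimen or intervention; "otherwise, they will not be allowed to continue participation".

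Two other places bear on these rules. Detail description defines control care as normal hospital care, "including physical rehabilitation when needed". Study participants and eligibility criteria covers a patient who, during the study, "presents any of the exclusion criteria and wishes to leave the study, they will be removed from the study".

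The article nowhere says that someone excluded under Detail description keeps the month 1, 3 and 6 assessments.

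**The concern.** Intention-to-treat needs outcomes from the people who were randomised, whether or not they completed the intervention. A rule that takes non-completers out of the study prevents those outcomes from being collected.

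Two features make this more than ordinary loss to follow-up. First, it is one-sided. A control who develops the same condition has no training to stop and stays in the study. Second, one trigger is ill health or injury, and the primary functional outcome (SPPB) measures balance, gait and leg strength. Those removed from the intervention arm are therefore likely to be those who would have scored worst, while their counterparts in the control arm are still measured. That tilts the comparison towards exercise.

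This is a rule of conduct. A later analysis plan cannot recover visits that were never held.

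**Working it through.** **1. The passages side by side.**

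| Question | Detail description | Sample size and statistical analysis |
|---|---|---|
| What happens to someone who stops training or becomes unfit? | Excluded from the study | Analysed by intention-to-treat |
| Which arm can meet the trigger? | Intervention only | Both arms are compared |
| What replaces the missing outcome? | Nothing stated | No imputation |

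Training runs for 4 weeks and the first follow-up visit is 1 month after discharge. A patient excluded during training will often have no post-baseline SPPB at all. Such a patient drops out of the ANCOVA. The mixed model can keep the baseline value only by assuming the outcome is missing at random, and that is hard to defend when deterioration caused the exclusion.

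**2. The plan's own figure.** Inputs, all from Sample size and statistical analysis: SD 2.5, r = 0.6, difference 1 point, type I error 0.05 (taken as two-sided), power 90%, losses 20%.

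- Residual SD = 2.5 × √(1 − 0.6²) = 2.0.
- The normal formula gives n = 2 × (1.960 + 1.282)² × 2.0² / 1² = 84.1, so 85 per group. The plan says 87, where t-based power is 0.906.
- 87 / 0.8 = 108.75, so 109 per group and 218 in total.

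The sample size is sound. The 20% allowance protects power; it does nothing about which patients are lost.

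**3. Illustration of the bias.** These assumptions are not in the documents: no true effect; a fraction q = 10–20% of the intervention arm excluded; no matching exclusion in controls; and those excluded would have scored D = 1–2 SPPB points below those retained, after adjustment for baseline.

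- The mean of the whole arm is the retained mean minus q × D, so the retained patients overstate the arm by q × D. This gives 0.1 × 1 = 0.1 up to 0.2 × 2 = 0.4 points.
- SE = 2.0 × √(2/87) = 0.303.
- Rejection probability = 1 − Φ(1.96 − shift/SE) + Φ(−1.96 − shift/SE).

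| Shift (points) | Shift/SE | Two-sided false-positive rate |
|---|---|---|
| 0.1 | 0.33 | 6.3% |
| 0.2 | 0.66 | 10.1% |
| 0.3 | 0.99 | 16.7% |
| 0.4 | 1.32 | 26.1% |

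Using 87 in both arms sits awkwardly with one-sided exclusion. With 109 controls and 109 × (1 − q) intervention patients, the ends of the range are 6.5% and 28.5%, so this choice matters little.

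**4. How far it depends on baseline adjustment.** Suppose instead that the raw gap of 1–2 points is equally present at baseline, with equal SDs. The ANCOVA slope is then 0.6, and 1 − 0.6 = 0.4 of the gap remains.

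- Shift = 0.4 × (0.1 to 0.4) = 0.04–0.16 points.
- False-positive rate, with SE 0.303: 5.2% to 8.2%.

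The answer therefore turns on whether the excluded patients were already weaker at baseline or deteriorated afterwards. The health trigger covers conditions that develop during the intervention, which points to at least some later deterioration.

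**The case against.** The best defence is that the article never says collected data are deleted or that these patients leave the analysis set. On that reading the analysis remains intention-to-treat on available data, and the exclusions are part of the planned 20% losses. The health trigger is also limited to the 4-week intervention, and Data collection and management offers make-up sessions, so a missed session alone does not exclude anyone. All of this is fair, and it means the documents do not show a plan to discard data. It does not remove the problem: without later visits, the missing outcomes are selected by health in one arm.

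Three stronger readings are tempting, and the documents do not support them.

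- *That transfer to a rehabilitation clinic after randomisation forces exclusion.* Being "transferred to a rehabilitation clinic prior to home discharge" is listed as an eligibility criterion. Under Study design, "Patient recruitment will begin in 4 days after the surgical procedure", so the destination may well be unsettled at randomisation, but no interval between randomisation and discharge is given. For a criterion met during the study, removal also requires that the patient wishes to leave.
- *That controls given usual-care rehabilitation are removed.* Rehabilitation within allocated usual care is not clearly another regimen. The wording is loose, but removal of these controls is not shown, so an opposing bias from that source cannot be claimed.
- *That 6–26% is a forecast.* No document gives an exclusion rate or an outcome gap.

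**Conclusion.** The point holds for the sentence on stopping or becoming unfit for training. As written, it excludes participants from the study after randomisation, applies in practice to one arm, is partly triggered by ill health, and conflicts with the stated intention-to-treat analysis. The likely direction of bias from this rule is towards exercise.

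Its size cannot be derived from the documents. Under the assumptions in the working it is 0.1–0.4 points against a target of 1 point, with a false-positive rate of about 6–26%. The rate is about 5–8% if baseline SPPB already carries the gap.

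Two secondary inconsistencies need reconciling but do not carry the finding. The ban on other structured exercise is not squared with usual-care rehabilitation. And the eligibility section makes removal depend on the patient's wish, whereas Detail description excludes unconditionally.

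Because the rule affects the primary comparison and lost visits cannot be recovered, it should be corrected while recruitment is open, as the article reports it to be.

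**What to change.** Amend Detail description so that stopping training, for whatever reason, or joining another exercise regimen is recorded with its date and reason and does not end study participation. State that all randomised participants keep the month 1, 3 and 6 visits and are analysed in their allocated arm, and that only withdrawal of consent to follow-up ends data collection. Align the removal sentence in Study participants and eligibility criteria with this, and say whether usual-care rehabilitation falls under the rule on other exercise. Rules on who stops training are untouched.

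The cost is a wording amendment and follow-up at visits already scheduled; the total stays at 218. The effect estimate will be somewhat diluted by patients who did not complete training. Deaths and consent withdrawals will still leave some outcomes missing, so the amendment removes this source of selection, not every source.

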### Randomization and blinding

The study participants will be randomized into an intervention group and a control group following a simple randomization procedure with a 1:1 allocation through a computer system (www.randomizer.org). The doctor who decides the inclusion in the intervention or control group will not be the attending physician, and the assessment staff will be blinded to the participant randomization assignment. It will not be possible to conceal the group assignment from the staff involved in the training of the intervention group. Due to the nature of the study, patients may not be blinded as to the group to which they belong.

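### Patients in either group who take up other structured exercise are removed from the study, which conflicts with the planned intention-to-treat analysis

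*Protocol article*

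**What the plan says.** The rule is in the protocol article under Detail description, in the last paragraph after Table 1. Both groups are asked not to take part in "another structured exercise regimen or intervention over the course of their participation; otherwise, they will not be allowed to continue participation". The sentence before it excludes from the study participants who want to stop training or who can no longer exercise safely.

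The section Sample size and statistical analysis sets out the analysis:

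- The principle: "Data will be analyzed using an intention-to-treat approach".
- Missing data: "The outcome variables will be analyzed using mixed models, without missing data imputation".
- The efficacy model for quantitative outcomes is ANCOVA, "using post-intervention value as dependent variable, group study as the principal effect and pre-intervention value as covariate".
- The loss allowance: "Assuming losses of 20%, the final objective of the size of each group is 109 patients".

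Three other statements bear on the point. Under Study participants and eligibility criteria, a patient who "presents any of the exclusion criteria and wishes to leave the study, they will be removed from the study"; there, removal also needs the patient's wish. Under Randomization and blinding, "patients may not be blinded as to the group to which they belong". Under Detail description, controls receive "normal hospital care based on the Enhanced Recovery After Surgery (ERAS) protocol [31], including physical rehabilitation when needed". Outcomes are scheduled at the initial visit and at months 1, 3 and 6 after discharge.

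**The concern.** Intention-to-treat needs two things: patients are analysed in the group to which they were assigned, and they are followed so that there is something to analyse. Outside exercise happens after randomisation, may depend on the assigned group, and is likely to affect SPPB, the outcome on which the trial is sized. A rule that ends participation on that ground stops the data that the analysis principle relies on.

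Removal may well be unequal between groups. Patients are unblinded and controls are offered no programme, so controls have more reason to look for exercise elsewhere. The remaining controls would then be a selected group, and the comparison would drift from intention-to-treat towards a comparison of compliers. If the removed controls are the fitter or more motivated ones, the effect is overstated. If they are weaker patients who were advised to exercise, it is understated. The article gives no basis for choosing between these.

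**Working it through.** **1. What the rule does.** It covers both groups. Patients in the intervention group could in principle lose their training and still be followed. Controls have no study training to lose, so for them the end of participation is the end of study membership. Nothing in the article says that removed patients are still assessed.

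**2. What the analysis then has.**

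- *ANCOVA* needs a post-intervention value. A patient removed before month 1 has none and is not in the model.
- *The mixed model* uses visits before removal only and relies on the later values being missing at random. It is valid if the earlier values explain the removal, and not otherwise.
- *No imputation* is not a fault in itself. It means only that nothing else replaces the uncollected values.

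**3. The plan's own sample size.** Inputs from the statistical section: SD 2.5, pre-post correlation 0.6, difference 1 point, type I error 0.05 (taken as two-sided; the article does not say), power 90%, ANCOVA.

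- Residual variance = 2.5² × (1 − 0.6²) = 6.25 × 0.64 = 4.0, so residual SD = 2.0.
- Normal approximation: n = 2 × 4.0 × (1.960 + 1.282)² / 1² ≈ 84.1, so 85 per group. The noncentral t gives 86. The stated 87 is reproduced to within two patients.
- Losses: 87 / (1 − 0.20) = 108.75, so 109 per group and 218 in total, as stated.
- Allowance: 109 − 87 = 22 losses per group.

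**4. Precision.** The article gives no removal rate. Assume 1% to 10% of 109, that is 1.1 to 10.9, or about 1 to 11 patients per group. Power is taken from the noncentral t with n₁ + n₂ − 3 degrees of freedom and noncentrality 1 / (2.0 × √(1/n₁ + 1/n₂)).

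| Situation | n₁, n₂ | Noncentrality | Power |
|---|---|---|---|
| Removals within the 20% allowance | 87, 87 | 3.30 | 0.906 |
| 1% removed on top of a full 20% loss (87 − 1) | 86, 86 | 3.28 | 0.903 |
| 10% removed on top of a full 20% loss (87 − 11) | 76, 76 | 3.08 | 0.865 |
| The same 10%, from controls only | 87, 76 | 3.18 | 0.886 |

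**5. Bias.** If a fraction *f* of one group is removed, and those patients would have differed from the rest of the group by *D* points, the observed mean of that group is off by *f* × *D*. Neither quantity is in the article. Purely as illustration, with removal in one group only, *f* from 5% to 20% and *D* from 1 to 2 points, the shift runs from 0.05 × 1 = 0.05 to 0.20 × 2 = 0.40 points, against a target difference of 1 point. It is smaller where baseline explains part of *D*, and about zero if nobody takes up other exercise or if earlier values explain the removal. This shows how the bias scales; it is not an estimate.

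**The case against.** The best counter-argument is that loss of outcome data is inferred. The article says that these patients may not continue; it does not say that their assessments stop or that their data are discarded. It condenses a full protocol that is available on request, and follow-up after discontinuation is often described there. This would carry weight if the complaint were an omission. The complaint is about a rule that the article states, which for controls has no other natural meaning, and nothing in the article qualifies it. An analysis plan cannot recover visits that were never made.

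Several other points stand, and limit the weight of the finding:

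- Limiting contamination is a legitimate aim. The request to avoid other exercise serves it; removal is not needed.
- The mixed model is valid under missing at random, and the ANCOVA loss affects only patients removed before the post-intervention visit.
- Patients aged 70 or over recovering from urgent abdominal surgery may seldom join structured programmes. If so, the bias is small, but so is the dilution from keeping them.
- Removed patients would ordinarily count within the 20% allowance, so power is not the issue.
- The wish-to-leave condition covers a different event, so the contrast with it shows a milder rule in the same protocol, not a contradiction.
- The preceding sentence is arguably the clearer threat, since stopping training can occur in one group only. It has the same fault and should be corrected together with this rule, as one issue.

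Rehabilitation within usual care is, on the ordinary reading, allowed. The rule does not say so for rehabilitation prescribed after discharge, but the finding does not depend on that.

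**Conclusion.** The concern holds. The article ends study participation because of post-randomisation behaviour, in both groups and regardless of the patient's wish, while it promises an intention-to-treat analysis with no imputation. The conclusion rests on reading the end of participation as the end of follow-up.

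The problem is possible bias of unknown direction and size, not loss of power: power stays near 91% within the planned losses, and is about 86% in the least favourable case assumed in the table. It is a point to consider rather than a fatal flaw. It is worth acting on because the correction is cheap and because outcomes that go uncollected may not be recoverable.

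**What to change.** Replace the removal clause with wording such as:

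> Participants are asked to avoid other structured exercise programmes. Rehabilitation prescribed as part of clinical care is allowed in both groups. Participants who take up other exercise remain in the study, are assessed at months 1, 3 and 6, and are analysed in their assigned group.

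Treat the preceding sentence in the same way: when a patient stops training or can no longer exercise safely, stop the training and keep the follow-up. Record outside exercise as a protocol deviation. If the effect in the absence of other exercise is of interest, report it as a sensitivity analysis.

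The cost is a protocol amendment while recruitment is open, with the registry update and, if relevant, the information to current participants that the article already foresees. No patients or visits are added, because the assessments are already scheduled. There are two drawbacks: controls who exercise will dilute the contrast somewhat, and values for patients already removed may be lost.
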